**Methods:**

Individuals with overweight/obesity who do not habitually consume a MED dietary pattern will complete a 16-week randomized, multi-intervention, semi-controlled feeding study of isocaloric dietary interventions: (1) MED-amplified dietary pattern, containing 500 kcal/day from eight MED target foods: avocado, basil, cherry, chickpea, oat, red bell pepper, walnut, and a protein source (alternating between salmon or unprocessed, lean beef), and (2) habitual/Western dietary pattern, containing 500 kcal/day from six non-MED target foods: cheesecake, chocolate frozen yogurt, refined grain bread, sour cream, white potato, and unprocessed, lean beef. After a 2-week washout, participants complete four, 4-week intervention periods, with biospecimen sampling and outcome assessments at baseline and at intervention weeks 4, 8, 12, and 16. The primary outcome is change in the relative abundance of FSCs from the eight MED target foods in participant biospecimens from baseline to the end of each intervention period. Secondary outcomes include mean change in cardiometabolic health indicators, inflammatory markers, and adipokines. Exploratory outcomes include change in diversity and community composition of the gut microbiota.

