Diets were designed to incorporate target foods identified from previous metabolomics analyses of 100 foods consumed within a completed MED controlled feeding intervention and representing distinct food groups emphasized (mini-MED) or limited (Western) in a MED dietary pattern. Our preliminary data suggest these foods contain FSCs that are detectable in participant biospecimens after consumption (Table 1). Furthermore, we selected foods that are widely accessible and available year-round and in combination will provide adequate energy to achieve 500 kcal/day. Total energy intake of approximately 3500 kcal/week (500 kcal/day) from these foods is provided. During the mini-MED intervention, participants are provided fresh conventionally-grown avocados, basil, red bell peppers, and beef (both ground 90% lean and beef tenderloin); frozen sweet cherries and Atlantic, farm-raised salmon; canned chickpeas; dried basil and old-fashioned oats; and shelled, unsalted walnuts. During the Western intervention, participants are provided New York style cheesecake and regular sour cream, fresh white potato and beef (both ground 90% lean and beef tenderloin), refined grain rolls, and chocolate frozen yogurt bars. Serving sizes and number of servings per week are determined using the US Dietary Guidelines 2020–2025 [24] and serving size information in the United States Department of Agriculture (USDA)-supported food composition database, FoodData Central (Table 2). Dietary interventions are isocaloric and are not designed to fully replace participants’ usual diets; participants are instructed not to change other aspects of their diet aside from accounting for the 500 kcal/day of foods provided. Participants are asked to refrain from consumption of target Western foods when on each mini-MED intervention and vice versa.

**Table 1 Tab1:** Number of food-specific compounds detected in food and plasma for target foods in mini-MED study

Food group	Food	Compounds detected in food	Compounds detected in plasma
*mini-MED target foods*			
Fruit	Cherry	207	30
Fruit/vegetable	Avocado	1446	136
Vegetable	Red bell pepper	283	27
Herb	Basil	204	112
Nut	Walnut	313	23
Legume	Chickpea	41	17
Whole grain	Oat	185	10
Seafood^a^	Salmon	508	143
Lean meat^b^	Beef	276	76
*Western target foods*			
Red meat	Beef	276	76
Starchy vegetable	White potato	19	0
High-fat dairy	Sour cream	271	8
Sweets/dessert	Chocolate frozen yogurt	467	27
Sweets/dessert	Cheesecake^c^	N/A	N/A

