#### Sample size {14}

Most of our planned analyses use each individual as their own control by looking at the change over each dietary intervention period. This reduces between subject variability compared to a cross-sectional analysis and increases the statistical power at a given sample size. To obtain a reasonable minimum expected effect size for the mean difference divided by the standard deviation of the difference (i.e., Cohen’s *d* effect size), we used our analysis of salmon FSCs [13]. The minimum salmon FSC effect size that passed an FDR adjustment was 0.45. Using a paired *t*-test after consuming the food, a sample size of *N* = 20 was needed to achieve 80% power for this effect size of 0.45 and a Bonferroni multiple testing adjustment for the number of compounds that increased in the preliminary MED data (*N*_compounds_ = 21; *p*-value_adjusted_ = 0.05/21 = 0.0024). We assume a 10% loss to follow-up based on our experience in similar dietary intervention trials and therefore enroll *n* = 22 eligible individuals to have *n* = 20 individuals complete the trial.

We also evaluated the power of *N* = 20 sample size further using the Bonferroni adjustment for the 21 compounds that increased after consumption of the preliminary Mediterranean diet foods (*p*_adj_ = 0.0024) and a stricter adjustment using all 355 compounds that were detected in the MED foods and plasma (*p*_adj_ = 0.05/355 = 0.00014). For both significance thresholds, we achieve power across a range of relevant effect sizes (Fig. 2) including nearly 100% power to detect an effect size of 0.75 (the median effect size for the salmon FSCs that passed the FDR threshold).

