**Fig. 2 Fig2:**
[figure not shown]
Power calculation for mini-MED clinical trial. Power (*y*-axis) for *N* = 20 for a paired *t*-test of the difference between post- and pre-consumption of a food. Power was evaluated over various effect sizes (*x*-axis, mean difference/SD of difference) for three significance thresholds: nominal threshold of 0.05 (yellow), Bonferroni corrected threshold for 21 compounds that increased after consumption in the initial study (*p* = 2.4e − 3), and Bonferroni corrected threshold for 355 compounds that were detected in MED foods and plasma (*p* = 1.4e − 4)

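### The 355 compounds behind the strict Bonferroni threshold are the Table 1 subtotal for the seven plant foods; salmon and beef are left out

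*Protocol article*

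**What the plan says.** The Sample size section justifies N = 20 with a Bonferroni threshold for 21 compounds (0.0024). It then evaluates the same N under "a stricter adjustment using all 355 compounds that were detected in the MED foods and plasma", with a threshold of 0.05/355 = 0.00014. The Fig. 2 legend labels one power curve as the "Bonferroni corrected threshold for 355 compounds that were detected in MED foods and plasma".

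The Methods paragraph of the abstract lists the foods concerned as "eight MED target foods: avocado, basil, cherry, chickpea, oat, red bell pepper, walnut, and a protein source (alternating between salmon or unprocessed, lean beef", and defines the primary outcome as "change in the relative abundance of FSCs from the eight MED target foods in participant biospecimens". The protein source is therefore one of the eight.

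Table 1, titled "Number of food-specific compounds detected in food and plasma for target foods in mini-MED study", gives a plasma count for each food. Salmon (143) and beef (76) stand under its mini-MED heading together with the seven plant foods.

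**The concern.** The strict threshold is offered as the conservative check on the sample size, and the text describes its divisor as all compounds found in both the MED foods and plasma. Adding the relevant column of Table 1 does not give that number. If the divisor leaves out foods that belong to the primary outcome, the check is less strict than described, and the power curve drawn at that threshold is slightly too favourable. The effect sizes used with it (0.45 and 0.75) come from salmon compounds, and salmon is one of the foods left out.

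**Working it through.** **Inputs** (Table 1, compounds detected in plasma, mini-MED target foods): cherry 30, avocado 136, red bell pepper 27, basil 112, walnut 23, chickpea 17, oat 10, salmon 143, beef 76.

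**Reproducing the plan's figure**

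- Seven plant foods: 30 + 136 + 27 + 112 + 23 + 17 + 10 = 355.
- Threshold: 0.05/355 = 0.000141, which rounds to the stated 0.00014. The division is right.
- Of all subsets of the nine foods, only one other sums to 355: avocado, salmon and beef (136 + 143 + 76). It has no evident rationale.

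**Adding the protein source**

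- Both sources: 355 + 143 + 76 = 574; 0.05/574 = 0.000087.
- Salmon only: 355 + 143 = 498; 0.05/498 = 0.00010.
- Beef only: 355 + 76 = 431; 0.05/431 = 0.00012.
- Share left out against the full list: 219/574 = 38%.

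Adding the counts assumes that no compound is counted under two foods. This fits the term food-specific, and the seven plant counts reach 355 with no deduction for overlap.

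**Effect on power**

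Paired t-test, N = 20, 19 degrees of freedom. The plan does not state sidedness, so two-sided is an assumption. The noncentrality parameter is d√N; for d = 0.75 it is 0.75 × √20 = 3.354. Power is the probability that a noncentral t with this parameter exceeds the critical value at alpha = 0.05/m.

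| m | alpha | critical t | power at d = 0.75 | d for 80% power |
|---|---|---|---|---|
| 355 | 0.00014 | 4.75 | 14.5% | 1.28 |
| 431 | 0.00012 | 4.83 | 13.2% | 1.30 |
| 498 | 0.00010 | 4.90 | 12.3% | 1.32 |
| 574 | 0.000087 | 4.96 | 11.4% | 1.33 |

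One-sided, power at d = 0.75 moves from 20.2% (m = 355) to 16.1% (m = 574).

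**The case against.** **574 is not the only defensible family.** Each mini-MED period has one protein source, so a pre/post test over a single period involves 498 or 431 compounds. There is also an argument for setting beef aside. It is eaten in both Western periods, and the Objectives expect its compounds to stay stable across dietary backgrounds, whereas the Statistical methods section validates a compound by a rise on mini-MED and a fall on Western. This stands: the documents do not single out 574 as the one correct count. It does not rescue 355, because it gives no reason to drop salmon, and the text claims to cover all the MED foods.

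**The count drives no decision.** N = 20 is derived from the 21-compound threshold. The planned analysis controls FDR over the number of FSCs, and compounds are first filtered for missingness and QC variability, so Bonferroni with 355 is never applied to trial data. This stands in full. A reader might infer that the trial's primary tests will run at too lenient a level; the documents do not support that.

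**Borrowing an effect size from salmon is legitimate.** The plan uses it only as a plausible minimum effect, and such a value need not come from the family being tested. This also stands. It is awkward that salmon supplies the effect and is missing from the divisor, but that is not an error in itself.

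**Conclusion.** The text and the Fig. 2 legend contradict Table 1. The number 355 is the plant-food subtotal, not the count for all MED target foods. That the two protein foods are what was left out is an inference, but the subtotal matches exactly and no section restricts the count to plant foods.

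The consequence is limited. Going from 355 to 574 lowers power at d = 0.75 by about three percentage points (two-sided) and raises the effect detectable with 80% power by 0.05. Neither the sample size nor the error control in the trial analysis changes.

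A reader might take the 14.5% above as the plan's own figure, or put the whole power shortfall down to the wrong count. Neither is right. The plan states power close to 100% at d = 0.75 for both thresholds. Under the same two-sided test, power is about 47% at 0.0024 and 14.5% at 0.00014, with the divisors exactly as written. That failure is a separate and larger error, and correcting the count would not mend it.

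**What to change.** Choose one of two corrections and apply it in both the Sample size section and Fig. 2:

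1. If the threshold is meant to cover all MED target foods, replace 355 with 574 and 0.00014 with 0.000087.
2. If it is meant for the plant foods, drop the claim to cover all compounds, state that 355 is the count for the seven plant foods, and give the salmon (143) and beef (76) counts separately.

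In either case, recompute the power quoted at the threshold that is kept. The cost of correcting the count is a few words and, under the first option, one redrawn curve. It requires no change to the design, the enrolment target or the analysis.

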**Fig. 2 Fig2:**
[figure not shown]
Power calculation for mini-MED clinical trial. Power (*y*-axis) for *N* = 20 for a paired *t*-test of the difference between post- and pre-consumption of a food. Power was evaluated over various effect sizes (*x*-axis, mean difference/SD of difference) for three significance thresholds: nominal threshold of 0.05 (yellow), Bonferroni corrected threshold for 21 compounds that increased after consumption in the initial study (*p* = 2.4e − 3), and Bonferroni corrected threshold for 355 compounds that were detected in MED foods and plasma (*p* = 1.4e − 4)

#### Recruitment {15}

Volunteers are being recruited from the Denver, CO metropolitan area. All participants are recruited using IRB-approved flyers posted on campus and at local community settings, the University of Colorado Anschutz Medical Campus Research Studies website, campus-wide email listservs, and ClinicalTrials.gov. Interested individuals may complete screening over the phone or by accessing a link to a screening questionnaire.

### Assignment of interventions: allocation

#### Sequence generation {16a}

All participants complete the mini-MED and Western dietary interventions twice each for four total intervention periods. Participants are randomized (1:1) to start either the mini-MED or Western dietary interventions, with subsequent assignment to the other upon completion of the first. A second randomization within the mini-MED arm is conducted to allocate participants to order of consumption of either salmon or lean, unprocessed beef as a protein source resulting in a total of four possible intervention orders (Fig. 1). Lean, unprocessed beef is consumed as the protein source in both Western intervention periods. A permuted block randomization scheme and stratification by sex has been generated and is utilized to ensure balance between intervention order and number of males and females. The allocation sequence was generated using computer-generated random number sequence in R using the *sample* command in *base* R package.

#### Concealment mechanism {16b}

Allocation of first intervention will take place after each consented individual is deemed eligible and enrolled. Participants are not notified of their intervention assignment until completion of baseline data collection.

#### Implementation {16c}

The randomization scheme is maintained and enacted by the study biostatistician, and participants are enrolled by the study coordinator after confirmation of eligibility.

### Assignment of interventions: blinding

#### Who will be blinded {17a}

Due to the nature of the dietary intervention, it is not possible to blind participants nor clinical trial staff responsible for carrying out the intervention, such as the study coordinator. Clinical trial staff are not blinded to the allocation sequence nor intervention assignment. However, outcome assessors responsible for data collection (e.g., assessment of vitals, anthropometrics, venipuncture) and those conducting clinical, metabolomics, and statistical analyses will be blinded, as all participants are provided, and all samples and data labeled with, a unique alphanumeric study identifier (ID) that is not associated with intervention order.

#### Procedure for unblinding if needed {17b}

Participants and clinical trial staff are not blinded; outcome assessors will remain blinded throughout the study.

### Data collection and management

#### Plans for assessment and collection of outcomes {18a}

As described above, during the eligibility/enrollment visit at the CTRC, participants complete informed consent and Health Insurance Portability and Accountability Act (HIPAA) authorization via the e-Consent framework in REDCap [23]. Those deemed eligible are provided materials by mail for at-home biospecimen sampling, including 24-h and spot urine collection containers, fecal collection kits, and items needed to transport the biospecimens to subsequent study visits for drop off. Future visits are also scheduled at this time. Participants complete data collection visits pre- and post- each dietary intervention period for a total of six in-person assessments (including eligibility/enrollment) over the duration of the 16-week intervention. The samples obtained and procedures conducted at intervention weeks 4, 8, and 12 will generate data that serve as both post-intervention data for the respective preceding intervention and pre-intervention data for the respective ensuing intervention. Mid-intervention phone calls with the study coordinator are conducted for each intervention period. Outcomes are assessed via standardized, self-report questionnaires that can be completed remotely or in-person at assessments at the CTRC as outlined below. Participants also complete several biospecimen collections throughout the study. Prior to each data collection visit, participants are asked to fast overnight (consume nothing except for water for a minimum of 12 h), to drink plenty of water the day before and morning of the visit, and to abstain from vigorous exercise and alcohol consumption for 48 h prior to the scheduled visit. Details regarding the sampling plan and data collection at each time point are outlined in Table 3.

##### Standardized, self-report questionnaires

Participants complete questionnaires remotely prior to or in-person at data collection visits.*A sociodemographic questionnaire* is completed at the eligibility/enrollment visit. General demographic information, including age, sex, race, income, and education is collected as part of this assessment. Estimated time to complete this survey is under 5 min.A *personal health assessment (PHA)* is completed at the eligibility/enrollment visit. Medical history is collected as part of this assessment. Estimated time to complete this survey is less than 10 min. Updates are collected in-person at the end of each 4-week intervention period to document changes in health data (e.g., change in medication, health status).*Physical activity patterns* are assessed via the Global Physical Activity Questionnaire at the eligibility/enrollment visit and participants are asked to confirm that physical activity habits will remain stable throughout the duration of the intervention [28]. This is a validated measure of leisure-time physical activity and sedentary time, with resulting data providing estimates of activity in minutes/day and in metabolic equivalents. This questionnaire is a recommended physical activity assessment included in the NIH-supported Accumulating Data to Optimally Predict obesity Treatment (ADOPT) Core Measures project and takes approximately 5 min to complete [29].*Dietary intake* is assessed via 3-day food records collected via the NIH-supported Automated Self-Administered 24-h (ASA24®) Dietary Assessment Tool, version (2022), developed by the National Cancer Institute, Bethesda, MD, USA. The ASA24® is a free, web-based tool that enables multiple, automatically coded, self-administered 24-h diet recalls and/or single or multi-day food records. Food records are employed in this study. Participants record three consecutive days of dietary intakes in real-time using this online tool at enrollment as well as pre-, mid-, and post- each intervention period. Time to complete these records varies based upon participant intakes. For pre- and post-intervention time points, participants align dietary intake assessment with biospecimen sampling, completing the final day of diet records the day prior to in-person assessment visits. Dietary data will be used to assess intake of target foods as well as overall dietary patterns such as adherence to the US Dietary Guidelines as measured by the Healthy Eating Index [30].*Satisfaction with each dietary intervention period* is assessed after each intervention using both open-ended and closed-ended questions to gauge participant barriers to adherence, likes and dislikes about the foods included, and reported likelihood of adopting dietary behaviors after cessation of the intervention. This evaluation takes less than 5 min to complete.*(Optional) evaluation of the EnteroTracker® upper gastrointestinal (GI) sampling device* is completed to assess participant experience with the device. This questionnaire probes for adverse events, side effects, and feelings of discomfort to assess feasibility and tolerability of the device. This evaluation takes less than 5 min to complete.

##### Anthropometrics and clinical assessments

Anthropometrics and clinical health indicators are assessed in-person at the CTRC pre- and post-each intervention period throughout the study as follows:*Height/weight/body composition*: Standing height is assessed only at enrollment visits using a standard wall-mounted stadiometer by trained study personnel using standard Centers for Disease Control (CDC) protocols [31]. Care is taken to ensure individuals are standing in the proper position for standing height assessment with shoes removed, and height is recorded to the nearest 0.1 cm. Fasting weight is assessed in-person pre- and post- each intervention period using a calibrated TANITA Body Fat Analyzer TBF-105 digital scale equipped with bioelectrical impedance (BIA), which noninvasively assesses body composition (TANITA Corporation of America, Skokie, IL, USA). Participants are also provided a Bluetooth scale for home use to monitor fasting weight weekly for the duration of the study. Participants are asked to wear a provided standard procedure gown and remove shoes for all body weight assessments, and body weight is recorded to the nearest 0.1 kg. Height and body weight are used to assess BMI in kilograms divided by the square of height in meters.*Waist and hip circumference*: Participant waist and hip circumference are completed pre- and post- each intervention period at in-person assessment visits at the CTRC using standard CDC protocols [31]. Participants are asked to stand straight with feet close together and hands resting at sides, wearing only light clothing. A plasticized tape measure is used to assess waist circumference between the costal margin and the iliac crest to the nearest 0.1 cm. Similarly, a plasticized tape measure is used to measure hip circumference at the maximum protrusion of the gluteus maximus. Three measurements for each circumference are taken and the averages recorded for analysis.*Blood pressure*: Standard clinical methods are employed by trained study personnel to assess blood pressure using a manual sphygmomanometer on the right side of the body in a seated position after 5 min of rest. Three measurements are taken and results averaged for analysis.

##### Biospecimen sampling

At monthly in-person assessment visits at the CTRC, participants complete several biospecimen collections:*Fasting blood draw*: Trained phlebotomists use standard sterile techniques to collect approximately 35 mL of venous blood into Vacutainer tubes with appropriate additives for specific tests (e.g., EDTA collection tubes for plasma analysis). Trace metal-free materials are used for all blood collection, processing, and storage. Samples are collected after 12-h fast at five time points throughout the intervention (pre- and post- each intervention). Samples will be used for analysis of specific outcome measures, including FSCs and cardiometabolic health indicators such as lipids, lipoproteins, inflammatory markers, and adipokines (described below). Blood collected for plasma carotenoid assessments is immediately covered with foil to protect from light and maintained on ice prior to processing.*24-h urine sample*: Participants are asked to collect a 24-h urine sample the day prior to each in-person data collection visit (aligning with the final day of 3-day diet record collection). Briefly, participants are asked to start collecting urine after their first morning void on the day prior to in-person visits. All urine is collected using the materials provided (toilet hat, pre-labeled and pre-weighed 4 L high-density polyethylene (HDPE) jug) after this time and up until the first morning void the morning of the assessment visit, representing a full 24-h period. Urine is stored in a cool, dark place or refrigerated in the participants’ home refrigerators at approximately 4 °C between voids. Participants record start and end times and dates prior to placing in the provided cooler with ice pack for transport to the CTRC. Total urine volume is determined by weight, and samples are processed immediately to separate into aliquots, frozen on dry ice, and transferred to longer-term storage at − 80 °C for planned batch analyses at study completion.*First morning void spot urine samples*: Participants collect 10–20 mL urine from their first morning void (FMV) for two days prior to and the morning of in-person data collection visits (including a small amount of urine not included within the 24-h urine sample) using a pre-labeled urine collection container. This aligns with days 2 and 3 and the day after 3-day diet record collection for a total of three FMV samples. Participants are asked to place their urine sample into their home freezer at approximately − 20 °C immediately after collection and to transport the sample in the provided cooler with ice pack to in-person visits at the CTRC. Samples are thawed on ice and processed immediately to separate into 2 mL aliquots and placed at − 20 °C prior to subsequent transport on dry ice to longer-term storage at − 80 °C for planned batch analyses at study completion.*Fecal sample*: As close as possible prior to each in-person data collection visit, participants are asked to collect stool into the provided toilet hat and transfer to a pre-labeled fecal collection container using the provided collection tool/spatula and gloves (EasySampler® Stool Collection Kit, ALPCO Diagnostics, Salem, NH, USA) after training by research personnel. Participants record collection times and dates and place samples immediately in a home freezer at approximately − 20 °C upon collection. Participants are advised not to collect samples if taking certain medications (e.g., laxatives, antibiotics) or if experiencing diarrhea. Participants transport samples to the CTRC in the provided cooler with ice pack. Samples are thawed and processed immediately to separate into aliquots, frozen on dry ice, and stored at − 80 °C for planned batch analyses at study completion.*Skin carotenoids*: Participant skin carotenoids are assessed noninvasively at each in-person assessment visit using the Veggie Meter® (Longevity Link Corporation, Salt Lake City, UT, USA), which is a research-grade instrument that detects and quantifies carotenoids in the skin through the use of pressure-mediated reflection spectroscopy [32]. Procedures follow the published recommendations for use of the Veggie Meter® in the research setting [32]. Briefly, participants are asked to wash hands with soap and water, and skin carotenoids are measured on the nondominant ring finger in triplicate. The average of three scan values, each lasting approximately 30 s, will be used for all analyses. Skin carotenoids have been validated against plasma carotenoids and used as a proxy for fruit and vegetable intake in several studies [33].*(Optional) EnteroTracker® upper GI sampling device*: The EnteroTracker® is a novel, minimally invasive device developed at the University of Colorado for sampling the proximal gut that allows for the capture of samples from the upper GI tract and thus permits monitoring and study of the duodenal and jejunal microbiome, metabolome, and nutritional biomarkers. Externally, the 2-cm capsule device contains a slim, non-absorbent tethering string extending out of its end. Internally, it is a composed of a proximal, tethering string and a distal, collection string that are of different thicknesses and textures. This device is FDA class 1 510(k) exempt and cleared for commercial use for GI sampling. Participants have the option to complete the EnteroTracker® sampling pre- and post- each dietary intervention. Those choosing to participate are asked to refrain from use of mouthwash the morning of the visit where the EnteroTracker® device will be used. Briefly, when the intact capsule is swallowed, the tethering string is taped to the cheek. As the capsule passes through the upper GI tract, it deploys the collection string along the length of the esophagus, stomach, duodenum, and jejunum. The collection string then gently rubs on the epithelial surface obtaining a liquid biopsy from the mucosa. Dwell time for the string assessment is at least 1 h and no more than 4 h. Upon retrieval through the mouth, geographic localization of string samples is identified by (1) position along the length of the string (esophagus 0–45 cm, stomach 45-–65 cm, duodenum 65–90 cm, jejunum > 90 cm), (2) colorimetric changes on the collection string associated with changes in pH, and (3) presence of bile staining as an objective indicator of localization in the small intestine. Samples of the collection string corresponding to each segment are processed for planned microbiome assessments (e.g., 16S rRNA gene profiling, metagenomics). Previous studies have shown the EnteroTracker® is easily performed by a research assistant and well tolerated by patients, preferred over endoscopy, and thus highly suitable for repeated, unsedated, clinical and research sampling [34].
